## ABBREVIATIONS AND DEFINITIONS OF TERMS

| Abbreviation | Definition                                  |
|--------------|---------------------------------------------|
| BZD          | Benzodiazepine                              |
| CDWH         | Carolina Data Warehouse for Health          |
| CDC          | Centers for Disease Control and Prevention  |
| CSV          | Comma-separated values                      |
| DME          | Diazepam milligram equivalents              |
| EHR          | Electronic health record                    |
| GEE          | Generalized estimating equations            |
| HCP          | Healthcare provider                         |
| ITS          | Information Technology Services             |
| MME          | Morphine milligram equivalents              |
| STEADI       | Stop Elderly Accidents, Deaths and Injuries |

## PROTOCOL SYNOPSIS

|                                                                     |                                                                                                                                                                                                                                                                                                                                                                                                                                                                                                                                                                                                                                                                                                                                                                                                                                                                                                                                                                                                            |
|---------------------------------------------------------------------|------------------------------------------------------------------------------------------------------------------------------------------------------------------------------------------------------------------------------------------------------------------------------------------------------------------------------------------------------------------------------------------------------------------------------------------------------------------------------------------------------------------------------------------------------------------------------------------------------------------------------------------------------------------------------------------------------------------------------------------------------------------------------------------------------------------------------------------------------------------------------------------------------------------------------------------------------------------------------------------------------------|
| Study Title                                                  | Implementation of a Deprescribing Medication Program to Evaluate Falls in Older Adults                                                                                                                                                                                                                                                                                                                                                                                                                                                                                                                                                                                                                                                                                                                                                                                                                                                                                                                     |
| Funder                                                       | Centers for Disease Control and Prevention                                                                                                                                                                                                                                                                                                                                                                                                                                                                                                                                                                                                                                                                                                                                                                                                                                                                                                                                                                 |
| Study Rationale                                              | Falls among older adults in the US account for 2.8 million injuries, 800,000 hospitalizations, and 28,000 deaths per year.  US medical costs associated with falls now total approximately \$50 billion.  More than 150 randomized trials document successful falls interventions.  Observational studies show consistent associations between falls and both opioids and benzodiazepines (BZD). Thus, it is widely accepted that fall-related morbidity and mortality could be reduced if systems were in place to identify and intervene in falls risk. Unfortunately, most physicians do not routinely screen older patients for falls  and with the shortage of physicians going into primary care, it is unlikely that screening will improve. Therefore, an educational intervention supporting screening for risk of falls and deprescribing of opioids and benzodiazepines may have a meaningful impact on the fall risk in an elderly population. |
| Study Objective(s)                                           | 
AIM 1: Use EHR data to inform outpatient clinics of older adults who are at high risk of falls due to the chronic use of opioids and/or BZDs. Once alerted, clinics will use a team-based approach to screen and plan falls interventions focused on deprescribing.
 
AIM 2: Develop and implement a proactive deprescribing medication guidance document with supporting resources (toolkit) for use with older adults on opioids and/or BZDs.
 
AIM 3: Evaluate (a) the utilization of the deprescribing toolkit in practice; (b) the satisfaction of clinic teams with the toolkit; (c) the impact of the toolkit on opioid and BZD exposure (primary outcome variable); (d) the rate of falls (secondary outcome variable).
                                                                                                                                                                                                                                      |
| Study Design                                                 | This mixed method study incorporates two distinct study designs. Focus groups will be used to inform the development and refinement of a deprescribing guidance document with supporting resources. This document will define the provider-focused educational intervention which will be tested using a cluster-randomized design . Eligible providers will be randomly assigned to intervention and control groups. Impact of the educational intervention on medication use and falls will be assessed using an longitudinal pre-treatment post-treatment design , with patients receiving care from control clinics serving as a quasi-equivalent comparison group. Data from clinics will also be supplemented by a web-based survey , which will be given twice: prior to the start of the study and after its completion.                                                                                                                                        |
| Subject Population key criteria for Inclusion and Exclusion: | Inclusion Criteria: To be eligible to participate in the study, clinics need to be affiliated with UNC HealthCare and have a patient population that includes patients 65 years of age or older. The educational intervention will target patients at least 65 years old and taking at least one opioid or benzodiazepine medication listed                                                                                                                                                                                                                                                                                                                                                                                                                                                                                                                                                                                                                                                         |

---

in the design section for > 6 weeks, indicating they are at high risk for falls.

To be eligible to participate in the patient focus group, participants need to be a patient in one of the intervention group clinics, 65 years of age and older, and taking at least one opioid or benzodiazepine chronically.

### **Exclusion Criteria**

Clinics that do not provide primary care services will be excluded from participating in the study.

Patients who exhibit signs of cognitive impairment or speech/hearing deficits that make obtaining informed consent and completing data collection activities difficult; patients undergoing active cancer treatment, receiving hospice care, or living in a skilled nursing facility; and non-English speaking patients will be excluded from participating in the patient focus group. Participants who do not wish to be audio-recorded during focus group sessions will also be excluded.

Patients who exhibit signs of cognitive impairment; are non-English speaking; or are undergoing active cancer treatment, receiving hospice care, or living in a skilled nursing facility will be excluded from the deprescribing intervention.

---

|                                                               |                                                                                                                                                                                                                                                                                                                                                                                                                                                   |
|---------------------------------------------------------------|---------------------------------------------------------------------------------------------------------------------------------------------------------------------------------------------------------------------------------------------------------------------------------------------------------------------------------------------------------------------------------------------------------------------------------------------------|
| Number Of Subjects                                     | Focus groups: 12 healthcare professionals and 12 patients.
Web-based survey: 120 healthcare professionals
Cluster-randomized trial: Total number of clinics (intervention & control): 20; Total number of patients (intervention and control): 3,000                                                                                                                                                                   |
| Study Duration                                         | Focus groups: two focus groups (120 minutes each)
Web-based survey: 1 survey, given twice: pre-study and post-study
Cluster-randomized trial: 1 year
The entire study is expected to last 4 years                                                                                                                                                                                                                   |
| Study Phases
Screening
Observation | Focus groups: Participants will sign a consent form prior to the start of the focus group session.
Web-based surveys: The surveys will include a written statement stating that their participation in the survey is voluntary and by completing the survey they are consenting to participate.
Cluster-Randomized Trial: Each clinic's 'study champion' will sign a consent form prior to the clinic's participation. |
| Safety Evaluations                                     | The risk from focus groups and web-based surveys is expected to be minimal. To monitor safety from the educational intervention, we                                                                                                                                                                                                                                                                                                               |

---

---

will include specific monitoring criteria in the educational intervention itself (e.g., monthly follow-up with clinic champions about the study), with specific instructions to alert study staff if any adverse effects of deprescribing are observed. Additionally, a study team member will reach out to all intervention clinics monthly to ask about potential safety risks related to deprescribing.

---

---

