## 1.2 Potential Risks and Benefits

There are three primary methods used for this study: focus groups, web-based surveys, and a cluster-randomized trial. The risks from focus groups and web-based surveys are minimal and primarily involve the possibility of loss of confidentiality and participants feeling uncomfortable.

The primary risk for the cluster-randomized study is potential withdrawal symptoms from discontinuation of opioids and BZDs. This risk is part of the standard of care associated with opioid and BZD management and is no greater than the normal risk experienced with standard patient care. The goal of this study is to better inform clinicians as to the fall-related risks associated with elderly patients' use of opioids and BZDs as well as best practices for tapering patients off opioids and BZDs without excess risk. If a clinician deems the falls-related benefit from reducing or stopping an opioid or BZD outweighs the risk associated with withdrawal, they can work with a patient to reduce or stop their medication. As such, potential benefits to the patient include a reduced risk of falls, which are associated with substantial morbidity and mortality in older adults.

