### **4.2 Screening/Baseline Visit Procedures and Observation Procedures for the Cluster-Randomized Trial:**

- (1) Randomize intervention and control clinics:** A list of clinics that are interested in participating will be compiled by the primary investigators. A member of the study team, [name], PhD, will use the random number generator built into SAS to randomize 10 clinics into treatment and 10 clinics into control groups. If the number of potentially eligible clinics exceeds 20, 20 clinics will be chosen at random, and this list will subsequently be divided into 10 random treatment clinics and 10 random controls. Results of randomization will be provided to the study coordinators, who will inform clinics of their status.

Data for all patients who meet inclusion criteria will be included in this analysis. This educational

intervention is intended to better inform providers in intervention clinics as to the fall-related risks associated with opioids and BZDs as well as best practices in deprescribing opioids and BZDs. A toolkit to support screening and deprescribing will also be provided to providers at intervention clinics. It is expected that providers will use this information to attempt deprescribing for any patients for whom they feel the benefits of deprescribing outweigh the risks. The study team will collect data from the EHR on all potentially eligible patients, regardless of any attempted deprescribing. The same data will be collected for patients who received care from treatment and control clinics.

**(2) Screen for risk of falling:** Intervention group clinics will be expected to screen all patients who appear on the baseline report for falls risk, questions if the patient has not already been screened previously, by using the STEADI screening questions. Each clinic will be allowed to determine how they will integrate these questions into the patient care process. Although the processes used to integrate the screening questions into patient care will vary across clinics, all clinics will be required to enter patient responses to the questions into the EHR, as is standard practice in all UNC HealthCare clinics.

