**(6) Training of Personnel.** All personnel at Intervention Group clinics will be required to take part in an educational training session, which will include information about the study's purpose, general processes, and available resources. The training session will include physicians, physician assistants, nurse practitioners, nurses, pharmacists, technicians, medical assistants, office managers, case managers and quality improvement officers. Following the training, clinic staff will be able to (1) administer the three STEADI screening questions to all older adults identified in the baseline reports generated by Epic EHR data; (2) identify patients who qualify for the deprescribing intervention; (3) provide patients education about the risks associated with opioid use, BZD use, and falls; and (4) utilize the toolkit and associated resources to effectively and safely deprescribe opioids and BZDs when warranted. Special emphasis will be placed on sharing non-pharmacological recommendations with patients as alternatives to medications associated with an increased risk of falling. Finally, we also will provide in the toolkit - for clinicians interested in learning more - primary literature and other resources related to deprescribing.

**(7)** Following launch of the study, continuous quality improvement processes will be initiated. Specifically, a postdoctoral fellow based in the central project office will contact each intervention clinic within one week of the implementation of the intervention, then monthly thereafter. The phone contact will enable clinic personnel to: (1) ask and have answered any questions they may have about study procedures and (2) report unforeseen issues that need to be addressed, including safety concerns related to deprescribing. The fellow will also conduct clinic site visits if needed to resolve unforeseen problems and maintain engagement and fidelity for the duration of the project.

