# **7 SAFETY MANAGEMENT**

The primary mechanism for safety monitoring will be monthly check-ins by a postdoctoral research fellow who is part of the study team. As a part of monthly check-in calls, the fellow will inquire about any reported adverse effects from opioid and BZD deprescribing, such as increased pain, anxiety and

trouble sleeping. The educational intervention will include instructions for providers to notify clinic staff of any adverse effects, such as withdrawal. Additionally, the instructions will state that the provider should notify the study team directly if any serious adverse events, such as seizures from BZD, occur.

Withdrawal symptoms are a normal and common result of deprescribing. Prescribers of these medicines are familiar with these symptoms, and additional information on withdrawal will also be included in the educational materials. Options for patients who experience adverse effects from deprescribing include contacting the nighttime call service, walk-in clinics, visiting the emergency department, and same-day service at providers' offices. These usual sources of care will be available to assist patients if the need arises.

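### Adverse effects of deprescribing are actively sought only in intervention clinics and are not among the EHR outcomes, so the trial gives no between-arm estimate of them

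*Protocol*

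**What the plan says.** **Where adverse effects are sought.** The Safety Evaluations row of the protocol synopsis states that the study "will include specific monitoring criteria in the educational intervention itself" and that "a study team member will reach out to all intervention clinics monthly to ask about potential safety risks related to deprescribing". Section 4.2, item (7), gives the schedule: a fellow "will contact each intervention clinic within one week of the implementation of the intervention, then monthly thereafter". Section 7 says that "The primary mechanism for safety monitoring will be monthly check-ins by a postdoctoral research fellow". It does not name the arm, but the synopsis and section 4.2 do. Its instructions to providers, including the one to report serious events straight to the study team, belong to the educational intervention.

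**What control clinics get.** Section 4.2, item (4), gives them general patient education materials only. No section provides for asking them about withdrawal, pain, anxiety, sleep or seizures.

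**What is measured in both arms.** Section 4.2, item (1), states: "The same data will be collected for patients who received care from treatment and control clinics". Section 5 defines the outcomes taken from the EHR: opioid and BZD dose, discontinuation, and falls (STEADI responses and visits for injurious falls).

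**What is said about risk.** Section 1.2 names withdrawal as the main risk of the randomized part and calls it "no greater than the normal risk experienced with standard patient care". The Data and Safety Monitoring Plan in the synopsis gives the usual-care nature of the intervention as the reason for having no monitoring board.

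**Who is told.** The synopsis puts the criteria in place "with specific instructions to alert study staff if any adverse effects of deprescribing are observed". Section 7 describes "instructions for providers to notify clinic staff of any adverse effects", with direct notice to the study team for serious events.

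**The concern.** The trial aims to make intervention clinics reduce and stop opioids and BZDs more often than control clinics (hypotheses in section 6.3). If it succeeds, more intervention patients go through a taper. Whether withdrawal, seizures or emergency visits rise with that is the natural counterpart to the efficacy question, and randomization offers a fair way to answer it. Safety information is nevertheless gathered in one arm only, and the two-arm data source is not directed at these events.

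At stake is the balance that a reader will want to draw at the end. A dose reduction could be reported with a between-arm estimate and interval, and the accompanying harm only as a list of reports from one arm. The premise that the intervention is usual care, on which the risk statement and the monitoring arrangement rest, could not be checked against the trial's own data.

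**Working it through.** The protocol states no safety event rate, margin or power, so there is no figure to reproduce. The check is a comparison of the text, followed by an illustration of what two-arm capture would give.

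**Step 1. Sources of harm information, by arm.**

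| Source | Intervention | Control |
|---|---|---|
| Contact within a week, then monthly (synopsis; 4.2 item 7; 7) | yes | none described |
| Monitoring criteria in the educational intervention (synopsis) | yes | not received |
| Provider reports, including serious events (synopsis; 7) | yes | instructions not received |
| EHR: dose, discontinuation (5) | yes | yes |
| EHR: falls (5) | yes | yes |
| EHR: withdrawal, seizure or other deprescribing harm | not defined | not defined |

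Only falls appear in both columns as something that could count as harm. Falls are also the expected benefit, and they do not stand in for withdrawal or seizure.

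**Step 2. Why the solicited reports cannot fill the gap.** Observed rate = true rate × share captured. Suppose that the true rate is 10% in both arms, with 80% captured in one and 40% in the other (all assumed). The observed rates are 0.10 × 0.80 = 8% and 0.10 × 0.40 = 4%, a ratio of 2.0 with no true difference. With 10% captured in controls the ratio is 8% / 1% = 8.0. With nothing sought from controls, no ratio can be formed.

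**Step 3. Precision if coded events were taken from the EHR in both arms.**

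- From the protocol: 3,000 patients (3.2), equal split and 20% attrition (6.4.1), 10 clinics per arm (4.2 item 1). Patients per arm: 1,500 × 0.8 = 1,200. Patients per clinic: 1,200 / 10 = 120.
- Assumed, because the documents give neither: a 2% event rate and an ICC of 0 to 0.05.
- Half-width ignoring clustering: 1.96 × √(2 × 0.02 × 0.98 / 1,200) = 0.0112, or ±1.1 points.
- Design effect: 1 + (120 − 1) × ICC. The half-width is multiplied by its square root.

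| ICC | Design effect | Effective n per arm | Half-width (points) | Rate detectable at 80% power against 2% |
|---|---|---|---|---|
| 0 | 1.00 | 1,200 | ±1.12 | about 4.0% |
| 0.01 | 2.19 | 548 | 1.12 × 1.480 = ±1.66 | about 5.2% |
| 0.05 | 6.95 | 173 | 1.12 × 2.636 = ±2.95 | about 8.8% |

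The last column uses a two-sided 5% test of two proportions with the effective sample size. An allowance for having only 20 clinics would widen the intervals somewhat.

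**Step 4. Reporting route.** The synopsis has any adverse effect alerted to study staff. Section 7 has any adverse effect notified to clinic staff, and only serious events notified directly to the study team. For a non-serious event, the first recipient differs between the two places.

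**The case against.** The strongest reply is that the protocol plans no comparison of the call data. The calls monitor the clinics that receive the intervention, and reports go to the principal investigator, who follows up with the prescriber. That is ordinary signal detection, and one-arm solicitation is not wrong for it. This stands: the calls are not at fault. The gap is that nothing else covers these events comparatively.

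Several stronger readings are tempting, and the documents do not support them.

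- *That harms are collected only through the calls.* Providers are also told to report adverse effects and to send serious events directly to the study team.
- *That no harms can be compared, or that controls contribute no harm data.* Visits for injurious falls are taken from the EHR, and falls are compared between arms.
- *That no rate can be formed.* The baseline report and the EHR data count the eligible intervention patients, so a crude reported rate is possible in that arm.
- *That the trial sets out to show that risk is no greater than in usual care.* Section 1.2 states a risk-benefit premise about withdrawal, not a hypothesis.

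It can also be said that a code list belongs in a statistical analysis plan, which is not at hand. Such a plan could indeed name coded events, but it could not recover reports that were never sought from controls. Section 5 of the protocol, which sets the outcomes, contains no deprescribing harm.

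On the reporting routes, a two-tier reading is possible: clinic staff first, then the fellow at the next call, with serious events going straight to the study team. The synopsis does not express those tiers, so the texts still need aligning, though this is a small edit.

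**Conclusion.** The point holds for adverse effects of deprescribing such as withdrawal and seizures. They are actively sought in the intervention arm only, and none is defined as an outcome from the data collected in both arms. Carried out on the protocol's text alone, the trial gives no between-arm estimate of them. The risk statement in section 1.2 and the reason given for having no monitoring board rest on a premise that the planned data cannot check.

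This does not touch the primary analysis or the falls analysis. It is a worthwhile and inexpensive improvement, and its yield should not be oversold. At an assumed 2% event rate the interval is about ±1.7 points (ICC 0.01) to ±3.0 points (ICC 0.05), which at the upper end exceeds the event rate itself. Such data could reveal a large excess but would hardly establish that risk is no greater. The figures rest on the protocol's 3,000 patients, 20 clinics and 20% attrition, and on the assumed rate and ICC.

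**What to change.** 1. Add to the existing two-arm EHR extraction a prespecified list of coded events: emergency visits, hospitalisations, withdrawal, seizure, overdose and death. Use the same 12 months before and after index in both arms; death can be counted after index only.
2. Report each by arm, with a between-arm difference and a confidence interval that accounts for clustering by clinic.
3. State that the monthly calls and provider reports are descriptive signal detection for the intervention arm and will not be compared with controls.
4. Reconcile the synopsis and section 7 on who is to be told of an adverse effect, and when.

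The cost is a code list, a few tables and one aligned instruction; no new contact with patients or clinics is needed. There are three downsides. Coded events miss milder symptoms such as increased pain, anxiety or poor sleep. Coding of withdrawal may itself differ by arm, because only intervention staff receive the training. All-cause emergency visits, hospitalisations and death depend less on that training and are the safer comparison. Finally, precision is limited, as shown above.
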